#### Sample size

2.3.2

The sample size has been calculated based on the results of the multicenter study ‘PROA-SENIOR’ (13). Considering an intraclass correlation coefficient of 0.21, a coefficient of variation between center for total antimicrobial consumption (the main variable) of 0.41, and an average of 110 residents per center, with an alpha risk of 5%, a power of 80%, and a detection of the effect size of 20%, the required sample size is 9 centers. Adding a 10% loss, the minimum sample size obtained is 10 NHs. For the wastewater analysis, three participating NHs will be selected.

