
**Table 2 tab2:** Indicators from the EduFAST study.

Indicator		Definition
Antimicrobial use indicators	Numerators	Monthly total Defined Daily Dose (DDD) of antimicrobials (ATC groups J01 + J02) Monthly DDD of specific antimicrobials (amoxicillin, amoxicillin/clavulanic acid, cefixime, other cephalosporins, azithromycin, clarithromycin, ciprofloxacin, levofloxacin, moxifloxacin, clindamycin, metronidazole, sulfamethoxazole/trimethoprim, fosfomycin trometamol, and other antimicrobials) Monthly number of total antimicrobial prescriptions (ATC groups J01 + J02) Monthly number of prescriptions of specific antimicrobials
	Denominator	Number of residents in the month
Clinical indicators	Numerators	Monthly number of hospital admissions Monthly number of hospital admissions due to infections Monthly number of hospital admissions due to adverse effects of antimicrobials
	Denominator	Number of residents in the month
Microbiological indicators	Numerators	Monthly number of extended-spectrum beta-lactamase-producing *Escherichia coli* isolates Monthly number of extended-spectrum beta-lactamase-producing *Klebsiella pneumoniae* isolates Monthly number of carbapenemase-producing *Enterobacteriaceae* isolates Monthly number of methicillin-resistant *Staphylococcus aureus* isolates Monthly number of multidrug-resistant *Pseudomonas aeruginosa* isolates Monthly number of multidrug-resistant *Acinetobacter baumannii* isolates Monthly detection of DNA or toxin for *Clostridioides difficile*
	Denominator	Number of residents in the month

The flowchart corresponding to the web platform menu, which can only be accessed by participating users is shown in Figure 2.

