#### Human samples

2.6.1

Clinical samples, such as urine, sputum cultures, percutaneous aspirations, and exudates, will be collected during routine clinical care when clinically indicated through the pre-intervention and intervention phases and analyzed in the laboratory of each participating center. To identify carriers of MDR bacteria (carrier screening samples), nasal swabs will be collected to detect MRSA and rectal or perianal swabs to detect ESBL- and carbapenemase-producing *Enterobacterales*, MDR *P. aeruginosa* and *A. baumannii*, from residents in centers participating in wastewater analysis. These screening samples will be collected quarterly by nurses from residents who have provided written informed consent, during the intervention phase, between the first and the last day of this phase. These samples will be collected using swabs, sent in a bacterial transport medium, and processed in the same way as clinical samples for the phenotypic study in the coordinator center’s laboratory.

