#### Wastewater samples

2.6.2

For the analysis of wastewater in the selected NHs, a sample of between 500 and 1,000 mL will be collected from the drainage manhole of each center once a month between 8:00 and 10:00 a.m. A total of at least 24 samples will be collected throughout the study (12 during the pre-intervention phase and 12 during the intervention phase). If a center has more than one drainage manhole, samples will be collected from all of them. These samples will be transported under refrigeration to the coordinating center. There, four 50 mL aliquots will be prepared: two will be used to determine the levels of antimicrobials and their metabolites, and the other two for the analysis of microorganisms and resistance genes.

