### Statistical analysis

2.9

A descriptive analysis will be performed. Continuous variables will be expressed as measures of central tendency and dispersion, such as mean ± standard deviation or median and interquartile range, depending on the distribution. Categorical variables will be expressed as absolute and relative frequencies.

Interrupted Time Series Analysis (ITSA) will quantify changes in the level (immediate effect) and trend (sustained effect) of outcomes associated with implementing the web platform, considering the study’s longitudinal and ecological nature. ITSA will be performed using a segmented regression model to estimate four parameters: baseline level, baseline trend, the change in level immediately following the intervention, and the change in trend following the intervention. Seasonal adjustment will be applied to those time series in which seasonality were detected. The model incorporates an autoregressive term to account for the autocorrelation present in the time series data. To assess variability and the overall effect across different centers, we will use a linear mixed model (LMM) for repeated measures that includes a random intercept for center. Potential confounders will be managed as fixed effects covariates. *Post hoc* comparisons of estimated marginal means will be performed with the Bonferroni correction applied to adjust for multiple comparisons.

We will evaluate the correlations between the presence of MDR microorganisms and their resistance profiles in wastewater, clinical, and carrier screening samples. We will also evaluate the correlations between antimicrobial concentrations in wastewater and consumption data from centers. We will assess the strength and direction of these correlations using the appropriate Pearson or Spearman correlation coefficient. Then, we will perform univariate and multivariable linear regression analyses to further explore the relationships.

All statistical analyses will be performed using two-tailed tests in IBM SPSS Statistics and R statistical software. A *p*-value of less than 0.05 will be considered statistically significant.

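### The wastewater correlations and regressions are specified without the center and serial-correlation terms that repeated monthly samples from three homes require

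*Protocol article*

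**What the plan says.** All references are to the protocol article.

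- **Units (2.3.2 Sample size):** "For the wastewater analysis, three participating NHs will be selected". No power or precision figure is given for this part.
- **Sampling (2.6.2 Wastewater samples):** taken "once a month between 8:00 and 10:00 a.m", with this count: "A total of at least 24 samples will be collected throughout the study (12 during the pre-intervention phase and 12 during the intervention phase". Also: "If a center has more than one drainage manhole, samples will be collected from all of them".
- **Consumption (Table 2 in section 2.4):** "Monthly total Defined Daily Dose (DDD) of antimicrobials (ATC groups J01 + J02", with the same monthly measure for individual drugs.
- **Carrier screening (2.6.1 Human samples):** "These screening samples will be collected quarterly by nurses from residents who have provided written informed consent, during the intervention phase".
- **Method (2.9 Statistical analysis):** "We will assess the strength and direction of these correlations using the appropriate Pearson or Spearman correlation coefficient", after which "we will perform univariate and multivariable linear regression analyses". The two-tailed 0.05 threshold applies to every analysis.

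The paragraph of 2.9 just before this, on the effect of the platform, includes an autoregressive term and a random intercept for center. Neither is repeated for the wastewater links.

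**The concern.** The standard p-values of Pearson, Spearman and ordinary linear regression treat each point as a separate piece of evidence. Here the points are monthly series from three buildings. Two features break that assumption.

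- **Center differences.** Size, plumbing, dilution and resident mix shift all of a home's values together. With three homes, a chance ordering of the center levels can look like an association supported by dozens of points.
- **Serial correlation.** Neighboring months in one home resemble each other, so even a single home's series holds less information than its length suggests.

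Several manholes add to this if each is entered as its own point, because all are set against the same center-month consumption.

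Two of the four aims in the Introduction concern these relationships, and the closing statement on wastewater as a surveillance tool draws on them. Too high an error rate would turn differences between three buildings, or shared drifts over time, into apparent evidence for that use.

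**Working it through.** **Plan's own figure.** There is none for the wastewater correlations. The 9 centers in 2.3.2 (10 after 10% loss) concern total consumption. One before-after variant reproduces them: (1.96+0.84)² × (0.41/0.20)² ≈ 33.0; times the design effect 1 + 109 × 0.21 = 23.89; divided by 110 = 7.16; plus 1 = 8.16, so 9. In this variant 0.21 acts as the clustering of residents within homes. Using it for monthly center values is therefore an assumption.

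**Number of points.** If the 24 samples are per center (the article does not say so, but monthly sampling of each home fits), there are 3 × 24 = 72 center-months. Quarterly carrier screening over a 12-month phase gives 3 × 4 = 12 center-quarters.

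**Error-rate model.** For center c and month t, consumption is x = √ICCx · a_c + √(1−ICCx) · e_ct, and concentration y is built likewise with independent a and e, so the true link is zero. Each e is AR(1) with parameter φ. The test is t = r√(df/(1−r²)), two-sided 5%, with df = 72 − 2 when pooled, 72 − 3 − 1 within center and 24 − 2 for one center. There were 20,000 runs per cell. The ICC of concentration and φ are not in the article and are varied.

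| Analysis | ICC of x / y | φ = 0 | φ = 0.3 | φ = 0.5 |
|---|---|---|---|---|
| Pooled Pearson, 72 points | 0 / 0 | 5% | 7% | 12% |
| Pooled | 0.21 / 0.05 | 7% | 10% | 16% |
| Pooled | 0.21 / 0.21 | 12% | 16% | 21% |
| Pooled | 0.21 / 0.50 | 22% | 25% | 31% |
| Pooled | 0.50 / 0.50 | 39% | 40% | 44% |
| One center at a time, 24 points | any of these | 5% | 7% | 11–12% |
| Within-center, three homes | any of these | 5% | 7% | 11–12% |
| Within-center, serial correlation removed | any of these | 5% | 5% | 5% |

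A separate simulation gave 22% for 0.21 / 0.21 at φ = 0.5 and 38% for 0.50 / 0.50 at φ = 0, hence the ranges quoted. The last row takes φ as known; estimating it will do slightly less well. For the 12 carrier points, pooled, with ICC 0.21 in both and φ = 0, the rate is 6%.

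**Precision.** Even with independent points, the smallest correlation detectable with 80% power is tanh(2.80/√(n−3)): 0.33 for 72 points, 0.55 for 24 and 0.73 for 12.

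**Time window.** If a single sample measures the month's exposure with reliability R, a true r is seen as r√R. For r = 0.60 and assumed R of 0.3, 0.5, 0.7 and 0.9, this is 0.33, 0.42, 0.50 and 0.57. A simple model shows why R cannot be fixed. Suppose courses last d days, average μ a month, and their rate varies with coefficient of variation v. With p = d/30, the correlation between monthly courses and residents on treatment on one day is √p · √[(1 + μv²)/(1 + pμv²)]. For an assumed d = 7:

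- constant rate: √(7/30) = 0.48
- v = 0.41, μ = 4.3: 0.483 × √(1.723/1.169) = 0.59
- v = 0.41, μ = 15: 0.483 × √(3.522/1.588) = 0.72
- v = 0.41, μ = 30: 0.483 × √(6.043/2.177) = 0.80

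None of d, μ or v over time is in the article; 0.41 is borrowed from its between-center figure.

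**The case against.** The strongest reply is that pooling is never stated. The text is compatible with separate coefficients per home, or with center among the unlisted covariates of the multivariable regression, and an article may leave such detail to the full plan. The authors plainly know about clustering: the Discussion relies on mixed models to handle center effects, and the Abstract lists mixed models and wastewater correlation in one sentence. The inflation also rests on assumed ICCs, and the work is described as exploratory and does not concern the main variable.

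Much of this stands. A reader might infer that the plan commits to pooling 72 points as independent; it does not say so, and the 12–39% figures (φ = 0) apply only if it does. The objection does not dispose of the point, however. The article states a method for these links rather than staying silent, and the named method allows for neither feature. Separate analyses remove the center part only: 7% at φ = 0.3 and 11–12% at φ = 0.5 remain. They also leave about four carrier-screening points per home.

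A reader might also infer that the monthly comparison is an error with a fixed ceiling of about 0.4 to 0.5 on any correlation. The article does not support this. That ceiling needs a constant course rate, while 2.9 itself allows for seasonality. Nor is the specimen a two-hour collection: it is a sample taken at some time within a two-hour window, from each manhole where there are several. Monthly consumption at the center is a legitimate reading of the stated aim.

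**Conclusion.** The concern holds for the analysis method. Section 2.9 names simple coefficients and linear regression for repeated data from three homes and does not carry over the terms it uses one paragraph earlier.

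If the homes are pooled, the nominal 5% becomes about 12% with an ICC of 0.21 in both variables, 16–22% with AR(1) of 0.3–0.5 as well, and 38–39% with an ICC of 0.5 and no serial correlation. It stays near 7% if one ICC is 0.05 and there is no serial correlation. If the homes are analyzed separately, it is 7–12% at AR(1) of 0.3–0.5. The ICC of concentrations, the transfer of 0.21 to monthly values and the AR(1) values are assumptions. Both center and serial terms are needed, because a within-center correlation alone still gives 11–12% at AR(1) 0.5.

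The time window is a limitation. It is expected to weaken true links, by an amount the article does not allow anyone to fix. The main consumption analysis is not affected.

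**What to change.** State in the analysis plan, before the wastewater data are analyzed:

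1. Manhole values are averaged within a center-month, so that each center contributes one point per month.
2. The simple Pearson or Spearman coefficient is replaced by a within-center (repeated-measures) correlation as the descriptive measure.
3. Inference rests on a regression with center as a fixed effect and AR(1) errors. P-values from the correlation alone are not used as evidence.
4. The conclusion is limited to association over time within three homes.
5. One sample on one morning is acknowledged as an imprecise measure of a month's exposure, so a weak or absent correlation does not show that there is no link.

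Where dated prescriptions are already available, add a sensitivity analysis with consumption in the days before each sampling, keeping the monthly total as the main exposure. The article does not show that the three homes can supply such dates, so this stays optional.

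The core change costs only wording and needs no new samples. The price is that between-center information is given up, which with three homes is little.

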## Discussion

3

The success of ASPs hinges on continuing education and motivating healthcare professionals, as well as periodically measuring specific indicators related to clinical outcomes, antimicrobial use, and microbial resistance. Currently, these tools are lacking in NHs, which hinders the training of professionals and the monitoring of these indicators (30). Against this backdrop, EduFAST is being developed to address this need by providing a web platform that will facilitate the training of professionals and the monitoring of key parameters for ASP teams. The development and implementation of EduFAST will contribute to the implementation of antimicrobial stewardship strategies and ultimately improve the health of NH residents.

The improvements in antimicrobial use, reductions in the incidence of infections caused by MDR microorganisms, and decreases in associated healthcare costs led by ASPs in hospitals and primary care supports the need to implement these programs in NHs (31, 32). For this reason, the Centers for Disease Control and Prevention have recommended the establishment of ASPs in these centers, backed by a set of general measures (6). In the Spanish context, the Spanish National Action Plan on Antimicrobial Resistance (PRAN) has established a specific line of work to design the framework and strategy for the implementation of ASPs in NHs (33).

A previous systematic review and meta-analysis conducted by the project’s research team concluded that ASPs could reduce antimicrobial consumption in this setting without negatively impacting hospital admissions or mortality. However, it should be noted that few studies met the necessary quality standards to draw definitive conclusions on this matter. All of the studies included in the review used clinical practice guidelines and educational strategies as ASP tools (8). However, only two of the studies applied information and communication technology (ICT) strategies (34, 35). This contrasts with the expert recommendation guidance document for ASPs published in 2023, which states that e-tools should be included in ASP interventions whenever possible and feasible to facilitate guidelines, clinical pathways, and post-prescription reviews. The efficacy and safety of ASP e-tools should be validated through cluster randomized control trials or adequately controlled quasi-experimental designs, and ASP e-tools should be available to prescribers (36). The EduFAST project has been designed to meet these recommendations and bridge the gap in ICT use in ASPs in NHs.

Among ASP studies that employed ICT strategies, there were webinars, posters, and pocket cards aimed at healthcare professionals, such as nurses, pharmacists, and prescribers, to reduce the unnecessary use of antimicrobials for uncomplicated cystitis among non-catheterized residents (34, 35). Similarly, the EduFAST project will design a free web platform for healthcare professionals in NHs. However, EduFAST will include innovative features such as text documents containing information from therapeutic guidelines and clinical cases presented in video format. Additionally, questionnaires will be administered to assess participants’ knowledge before and after viewing the educational materials. The educational material within the EduFAST project will encompasses ASP principles, preventive measures of infection, and the diagnosis and treatment of main infectious syndromes, with a particular emphasis on the most prevalent ones (urinary tract, respiratory tract, and skin and soft tissue infections). However, this is a distinct point because most studies have focused exclusively on urinary tract infections (34, 37, 38) and, to a lesser extent, respiratory tract infections (39).

To evaluate the impact of ASPs, previous studies have analyzed changes in the number of prescriptions or, less frequently, in the DDD as an internationally accepted measure of antibiotic use (8). Indicators of antimicrobial resistance are infrequently reported, and the outcomes vary among studies, although common outcomes include *C. difficile* detection, MRSA and/or MDR gram negative bacterial infections (13, 34, 40, 41). Similarly, clinical outcomes (e.g., hospitalization rates, mortality, and clinical adverse events) are reported in fewer than one-third of ASP studies in NHs, according to a recent systematic review (41). The EduFAST project will collect antimicrobial consumption, resistance, and clinical indicators, allowing for comparison with the results of previous interventions. But also, EduFAST project will aim to evaluate the environmental impact by studying the concentration of antimicrobials, MDR microorganisms, and resistance genes in wastewater. Currently, there is little evidence regarding the impact of antibiotic use on the microbiological composition of wastewater in NHs and the potential use of wastewater for surveillance purposes of antimicrobial consumption and microbial resistance (42, 43). This project will therefore provide relevant information on this subject and contribute an environmental indicator that has not been included in ASPs previously.

The primary limitation of the study is its quasi-experimental, before-and-after design. However, given the recommendations of national and international organizations to promote the implementation of ASP in all healthcare settings and the existing evidence of its positive impact, proposing a clinical trial with a non-intervention comparison group would raise significant ethical concerns. Another limitation is the heterogeneity among NHs, particularly with regard to size, resident profiles, infrastructure, and human resource availability. This could lead to variability in implementation and affect adherence to the recorded variables. For this reason, we have implemented a system of close monitoring and follow-up of platform usage metrics and indicators, as described in the Materials and Methods section. Second, linear mixed models will be used to evaluate the intervention’s impact and handle center effects in this multicenter study.

In conclusion, implementing this project involves developing an interactive web platform to facilitate professional training and enable monitoring of indicators related to antimicrobial resistance and use in NHs. This initiative is expected to generate significant health benefits, including reducing overall antimicrobial consumption in these settings, optimizing prescribing patterns by further limiting the use of broad-spectrum antibiotics, reducing infections caused by MDR bacteria and *C. difficile*, and facilitating ASP interventions in NHs. Wastewater analysis will provide insight into the correlation between antimicrobial consumption, microbial resistance, and the environment, exploring its potential use for surveillance.
